## Abstract

**Background:**

There is a high prevalence of smoking and high burden of tobacco-related diseases among low-income populations. Effective, evidenced-based smoking cessation treatments are available, but low-income smokers are less likely than higher-income smokers to use these treatments, especially the most comprehensive forms that include a combination of pharmacotherapy and intensive behavioral counseling.

**Methods/Design:**

The primary objectives of this randomized controlled trial are to compare the effects of a proactive tobacco treatment intervention compared to usual care on population-level smoking abstinence rates and tobacco treatment utilization rates among a diverse population of low-income smokers, and to determine the cost-effectiveness of proactive tobacco treatment intervention. The proactive care intervention systematically offers low-income smokers free and easy access to evidence-based treatments and has two primary components: (1) proactive outreach to current smokers in the form of mailed invitation materials and telephone calls containing targeted health messages, and (2) facilitated access to free, comprehensive, evidence-based tobacco cessation treatments in the form of NRT and intensive, telephone-based behavioral counseling. The study aims to include a population-based sample (N = 2500) of adult smokers enrolled in the Minnesota Health Care Programs (MHCP), a state-funded health insurance plan for low-income persons. Baseline data is obtained from MHCP administrative databases and a participant survey that is conducted prior to randomization. Outcome data is collected from a follow-up survey conducted 12 months after randomization and MHCP administrative data. The primary outcome is six-month prolonged smoking abstinence at one year and is assessed at the population level. All randomized individuals are asked to complete the follow-up survey, regardless of whether they participated in tobacco treatment. Data analysis of the primary aims will follow intent-to-treat methodology.

**Discussion:**

There is a critical need to increase access to effective tobacco dependence treatments. This randomized trial evaluates the effects of proactive outreach coupled with free NRT and telephone counseling on the population impact of tobacco dependence treatment. If proven to be effective and cost-effective, national dissemination of proactive treatment approaches would reduce tobacco-related morbidity, mortality, and health care costs for low income Americans.

**Clinical trials registration:**

ClinicalTrials.gov: NCT01123967

## Background

Tobacco use rates are alarmingly high in low-income populations. In the United States, 27.9% of adults living below the federal poverty level smoke cigarettes compared to 17% of adults at or above the poverty level [1]. About 34% of adult Medicaid enrollees currently smoke cigarettes, and racial/ethnic minorities and women are disproportionally represented in the Medicaid population [2]. Smoking rates in the uninsured population are similar to the Medicaid population and higher than the general population (32% compared to 16% for ages 18–65) [2]. Smokers with lower incomes are also less likely to use evidence-based smoking cessation treatments such as pharmacotherapy and counseling than smokers with higher incomes [3-8]. In an analysis of the 2000 National Health Interview Survey, among smokers who were attempting to quit, only 15.5% of Medicaid enrollees used a cessation aid compared to 25.4% of individuals with private health insurance [6]. Consequently, low income populations experience an excess burden of tobacco-related morbidity and mortality. Additionally, this group can least afford the cost of cigarettes (an average of $2017 per year in the US) [9].

Over the past decade, coverage for tobacco dependence treatments by federal-state Medicaid programs has improved, but significant limitations remain. For example, the number of state Medicaid programs providing some coverage for tobacco dependence treatment increased from 25 in 1998 [10] to 47 in 2009 [11]. However, in 2009, only 18 state Medicaid programs covered individual cessation counseling for all of their enrollees. Most programs also require co-payments for tobacco dependence treatments (over 70%) and many require prior authorization. In addition, knowledge of Medicaid coverage for tobacco dependence treatments is low among Medicaid enrolled smokers and their physicians. In a 2004 study of enrollees and physicians from two state Medicaid programs with full coverage for nicotine replacement therapy (NRT), only 21% of enrollees and 46% of physicians were aware of this coverage [12]. In a 2003 study of tobacco cessation coverage awareness among New York state Medicaid enrollees, only 7% of those surveyed were aware that their state Medicaid program covered NRT [13].

Both patient-level and provider-level factors contribute to disparities in use of tobacco cessation treatment. Current approaches typically depend on either a smoker’s initiative to actively seek treatment or a clinical encounter in which the provider has the time, willingness, and capacity to deliver quality smoking cessation care [8,14]. Low income smokers may be less likely to seek treatment because of significant life stressors that reduce their motivation to quit, lower levels of knowledge about the benefits of pharmacotherapy as well as unaware that their state Medicaid program covers these treatments [15-17]. In addition, low income smokers experience unique, significant barriers to health care access and are vulnerable to health care providers’ assumptions about lack of interest in quitting [18,19].

Effective strategies are needed to provide increased access to evidence-based tobacco treatments, especially for low-income populations. In this paper, we describe the study design and methods of a prospective randomized controlled trial testing a proactive tobacco intervention that is hypothesized to have greater population impact because it will 1) achieve wide reach and increase utilization of treatment (proactive outreach with offer of free NRT and easy access to telephone care) and 2) increase the effectiveness of treatment (by efficient delivery of free NRT and intensive behavioral counseling). This proactive tobacco treatment intervention integrates population-based and individual approaches to address both patient and provider barriers to providing comprehensive care [20].

## Methods

### Study design

We will examine the population impact of a proactive care intervention in a population-based sample of adult smokers enrolled in the Minnesota Health Care Programs (MHCP). MHCP is a state-funded health insurance plan, administered by the Minnesota Department of Human Services (DHS), for low income persons and families comprising two major publicly subsidized health care assistance programs: Medicaid and MinnesotaCare. MinnesotaCare is for Minnesota residents that do not have access to affordable health care coverage and funded by a state tax on Minnesota hospitals and health care providers, Medicaid and enrollee premiums. The proactive tobacco intervention being tested has two primary components: 1) outreach to current smokers in the form of tailored mailings and telephone calls, and 2) facilitated access to a free, comprehensive, evidence-based treatment for tobacco dependence in the form of NRT and intensive, telephone-based behavioral counseling. This proactive approach is designed to overcome the predominant barriers to smoking cessation treatment (provider-based, access to care, and psychosocial) experienced by low-income smokers. Further, to assess the population impact of smoking cessation treatment, we include all smokers, regardless of their interest in quitting or participation in the offered treatment. This is in contrast to studies designed to test the efficacy of an intervention in smokers who have indicated strong interest in quitting.

The study is a two group randomized controlled trial (see Figure 1) and was approved by the Institutional Review Boards at the University of Minnesota and the Minnesota Department of Human Services. The study population is stratified by age group (18–24, 25–34, and 35–64), by gender, and by healthcare program (Medicaid and MinnesotaCare). Stratified program enrollee data is obtained from MHCP administrative databases and a baseline participant screening survey conducted prior to randomization to assess current tobacco use as well as additional baseline information. Survey recruitment from the strata follows the proportions present in the MHCP enrollee population. Individuals reporting current tobacco use (defined as having smoked a cigarette in the past 30 days, even a puff) on the baseline survey with a valid home address, and an adequate proficiency in English to complete study surveys and participate in telephone counseling are randomized with equal likelihood to receive either 1) proactive outreach combined with free nicotine replacement therapy (NRT) and telephone counseling, or 2) usual (reactive) care available from primary care providers and/or existing telephone helpline programs. The target recruitment goal is 2500 current cigarette smokers.

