### Outcomes

The primary outcome is self-reported six-month prolonged abstinence [21] at one year assessed at the population-level (i.e., smoking abstinence among all smokers, including those who use and those who do not use treatment). A participant who smoked at least once on 7 consecutive days or at least once on 2 consecutive weekends in the six-month period is considered a treatment failure. The primary outcome for both groups is measured from the 12 month follow-up survey. Secondary outcomes include self-reported 7-day point prevalence and 30-day point prevalence, defined as having not smoked a part of a cigarette in the past 7 days and as having not smoked a part of a cigarette in the past 30 days, respectively. Following the Society for Research on Nicotine & Tobacco recommendations, biochemical verification of smoking abstinence has not been performed because of the low misreporting rates in large-scale, population based trials that have limited face-to-face contact with study staff [36].

Additional secondary outcomes include utilization of tobacco cessation treatment during the 12 month follow-up (from any source, including care from outside the study) specifically: 1) initiation of combined intensive behavioral counseling and medication treatment, 2) initiation of intensive behavioral counseling, and 3) initiation of medication treatment. These secondary outcomes are primarily assessed using self-report from the follow-up survey because smokers may seek care from outside the study due to the proactive strategies tested. Initiation of medication treatment is defined as using one or more tobacco dependence medications (e.g., NRT, bupropion or varenicline) in the 12 month follow-up period. Initiation of intensive counseling is defined as the completion of at least one call from a telephone counseling program or making at least one visit to a group or individual smoking cessation program in the 12 month follow-up period. In addition, we will assess tobacco dependence medication utilization by extracting pharmacy claims data from the MHCP claims administrative data and examine the prescription rates of individual medications, number of medications prescribed, and duration of medication use.

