### Sample size and power analysis

The power analysis assumes independent samples in the two groups within strata and considers a type one error rate of 0.05 for analysis of the primary outcome, six-month prolonged abstinence. The goal sample size for this study is N = 2500 (1250 per group), which accounts for a 40% nonresponse rate to the follow-up survey to ensure that we have observed smoking status outcome data on 1500 respondents (750 per group). The anticipated six-month prolonged smoking abstinence rate in the usual care arm is between 2% to 5%. This sample size provides over 85% power to detect intervention effects if the intervention raises abstinence rates by 4% and provides approximately 80% power or greater to detect differences if the intervention raises quit rates by 3.5%. The difference this study is powered to detect is of the same relative order of magnitude as those in prior smoking cessation clinical trials (e.g. odds ratios of 1.5 to 2.0) [49].

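### One puff in 30 days admits a participant, but the primary outcome's failure rule is much stricter, so an unchanged infrequent smoker can be counted as abstinent in either arm

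*Protocol article*

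**What the plan says.** Under Study design, entry is open to "Individuals reporting current tobacco use (defined as having smoked a cigarette in the past 30 days, even a puff) on the baseline survey" who also have a valid address and adequate English. No minimum number of days or cigarettes is set.

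Under Outcomes, "The primary outcome is self-reported six-month prolonged abstinence [21] at one year assessed at the population-level". Failure is defined there as follows: "A participant who smoked at least once on 7 consecutive days or at least once on 2 consecutive weekends in the six-month period" is a treatment failure. No quit attempt or change from baseline is required, and Study design ties follow-up to the start of the intervention, not to a quit date. A secondary outcome, 30-day point prevalence, requires that no part of a cigarette was smoked in the past 30 days.

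Under Sample size and power analysis, "The anticipated six-month prolonged smoking abstinence rate in the usual care arm is between 2% to 5" (per cent). Power is stated for rises of 4 and 3.5 points with 750 respondents per group. The section does not mention participants whose smoking at entry would already pass the outcome rule.

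Under Statistical analyses, the log odds of abstinence are modelled on intervention and strata only. The Smoking behavior subsection, within the survey measures labelled as potential moderators and confounders, says that smoking history and the Heaviness of Smoking Index are collected.

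**The concern.** The entry threshold and the failure threshold do not meet. Take a person who smokes one cigarette on a single weekday each week. That person is a current smoker at entry. With the same habit for a year, he or she never smokes on 7 consecutive days or on 2 consecutive weekends, and so does not meet the stated failure rule. For such a person the primary outcome does not measure cessation.

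At stake are the meaning of the abstinence rate in each arm, the size of the odds ratio and the power. The planned usual-care rate is only 2% to 5%, so even a small share of unchanged participants counted as abstinent would be large relative to the real quitters.

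**Working it through.** **1. Do the thresholds conflict?**

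- Entry: any cigarette in the past 30 days.
- Failure: smoking on 7 consecutive days, or on 2 consecutive weekends, in six months.
- Daily smokers and people who smoke every weekend meet both.
- People who smoke on scattered weekdays, or once or twice a month, meet the first and not the second.

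The gap is real but confined to infrequent or irregular smokers.

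**2. The plan's own figures.** Inputs from Sample size and power analysis: 750 respondents per arm, type I error 0.05 (taken as two-sided, since sidedness is not stated), usual care 2% to 5%, rises of 4 and 3.5 points. The nonresponse step reproduces: 1500/(1 − 0.40) = 2500. With the pooled-variance normal approximation,

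power = Φ{[d − 1.96·√(2p̄(1−p̄)/n)] / √([p₁(1−p₁)+p₂(1−p₂)]/n)}.

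For 5% versus 9%: d = 0.04, p̄ = 0.07, n = 750. The null standard error is √(0.1302/750) = 0.01318 and the alternative one √(0.1294/750) = 0.01314. So z = (0.04 − 0.02582)/0.01314 = 1.08 and power is 86.0%. For 2% versus 6% it is 97.7%. The stated figure of over 85% for 4 points is reproduced across the range. For 3.5 points, power is 94.7% at 2%, 83.0% at 4% and 77.1% at 5%, broadly as stated.

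**3. Effect of the gap.** Let q be the share of respondents who already pass the rule at baseline, do not change, and are counted as abstinent in both arms. The documents give no value, so q is an assumption. The rest quit at rates p and p + 0.04. The arm rates are then q + (1−q)p and q + (1−q)(p + 0.04).

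| Rest of sample | q | Usual care | Intervention | Difference (points) | Odds ratio | Power |
|---|---|---|---|---|---|---|
| 5% vs 9% | 0% | 5.00% | 9.00% | 4.00 | 1.88 | 86% |
| | 1% | 5.95% | 9.91% | 3.96 | 1.74 | 81% |
| | 2% | 6.90% | 10.82% | 3.92 | 1.64 | 76% |
| | 5% | 9.75% | 13.55% | 3.80 | 1.45 | 63% |
| 2% vs 6% | 0% | 2.00% | 6.00% | 4.00 | 3.13 | 98% |
| | 2% | 3.96% | 7.88% | 3.92 | 2.07 | 90% |
| | 3% | 4.94% | 8.82% | 3.88 | 1.86 | 84% |
| | 5% | 6.90% | 10.70% | 3.80 | 1.62 | 74% |

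**4. Where the loss comes from.** The risk difference shrinks only by the factor 1 − q. Most of the power loss comes from the higher event rate in both arms. If the 4 points are held fixed and q is simply added to both rates, power at 5% usual care is still only 77% at q = 2% and 66% at q = 5%.

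**5. Share of usual-care abstainers who changed nothing.** At q = 5% and 5% quitting among the rest, 0.05/0.0975 = 51%. At q = 2% and 2% quitting, 0.02/0.0396 = 51%.

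**The case against.** Several objections have force.

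- *The failure rule does not say that everyone else succeeds.* The outcome is self-reported prolonged abstinence under a cited definition, and the survey item is not shown. This stands: one can say that an unchanged infrequent smoker can be counted as abstinent, not that he or she will be.
- *The size is assumed, and q may be double counted.* The 2% to 5% is the rate anticipated in the usual-care arm, and nothing says that it leaves out light smokers. This stands. A reader might infer that the usual-care rate must exceed 5%. It need not: with 2% quitting among the rest and q = 3%, it is 4.94%.
- *Recent quitters.* A reader might infer that someone who stopped shortly before the survey is also a false success. That does not follow. If such a person stays quit, abstinent is the correct code, and the Telephone care subsection includes relapse prevention, so the intervention has something to offer.
- *Cost-effectiveness.* A reader might infer that the incremental ratio is distorted. Its denominator is a difference between arms, so people counted in both largely cancel, leaving only the factor 1 − q.
- *The plan already has a check.* The 30-day point-prevalence outcome catches the person who still smokes in each 30 days. This is true, but that outcome is secondary and does not repair the primary one.
- *The aim is population-level.* Including all smokers regardless of interest in quitting is deliberate, and it argues against making a restricted subset the primary analysis. It concerns motivation, however, and does not justify counting unchanged smoking as abstinence.

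**Conclusion.** The concern holds as a mismatch between the entry rule and the primary outcome's failure rule, affecting infrequent and irregular smokers only. It inflates both abstinence rates, attenuates the odds ratio and lowers power.

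The amount cannot be fixed from the documents. At the top of the planned usual-care range, an assumed share of 1% already takes power for 4 points below the stated 85%, and 5% takes it to 63%. At the bottom of the range, power stays at 90% with a share of 2% and falls to 74% with 5%. These figures assume that the people concerned do not change, are coded abstinent in both arms, and come on top of the quit rate among the rest.

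A reader might go further and infer a result biased in favour of one arm. The documents do not support that: allocation is random with equal likelihood, such people are expected equally in both arms, and the distortion is towards no effect.

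**What to change.** Three changes, all to the analysis text:

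1. Keep all randomised participants in the primary analysis, in line with the population-level aim.
2. Add baseline smoking intensity to the logistic model under Statistical analyses, using what the baseline survey already collects (smoking history, Heaviness of Smoking Index).
3. Prespecify a sensitivity analysis that excludes participants whose baseline pattern, as far as recorded, would not count as smoking under the failure rule. Read it beside 30-day point prevalence. Because the exclusion uses data collected before randomisation, the comparison stays randomised. If the group could be identified fully, the loss would be small: at q = 5%, 750 × 0.95 ≈ 712 per arm remain, and power for 5% versus 9% is 84%.

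The cost is slightly more analysis work and an odds ratio that is conditional on baseline smoking, to be reported as such. One limit remains: the article shows no item on consecutive days or weekends smoked, so the exclusion may have to rest on an approximation, which should be written down in advance.

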**Figure 1 F1:**
[figure not shown]
Study design.

Outcome data is being collected from a follow-up survey conducted 12 months after randomization as well as from the MHCP administrative data (e.g., pharmacy claims data) for the twelve months following randomization. Since this is a cessation-induction trial (i.e., evaluation of an intervention to encourage cessation among a population-based sample of smokers, including those not currently trying to quit), it is problematic to tie follow-up of cessation outcomes to multiple quit dates. The Society for Research on Nicotine and Tobacco (SRNT) Measures Workgroup recommends that, for cessation-induction trials, follow-ups should be tied to the onset of the intervention, as opposed to aid-to-cessation trials (e.g., efficacy trials of pharmacotherapy) which tie follow-up to the quit date [21].

### Usual care comparison group

All MHCP enrollees are assigned a primary care provider and usual care participants are able to see their provider to access smoking cessation treatment. However, depending on the primary care provider’s willingness and capacity to adhere to guidelines, tobacco treatment is variable, ranging from brief advice and medications to intensive counseling. Usual care participants also have access to smoking cessation medications at substantially reduced cost because MHCP provides insurance coverage for all recommended first-line nicotine replacement products (patch, gum, lozenge, inhaler, and nasal spray), as well as sustained-release bupropion and varenicline. However, an enrollee must obtain a prescription from a provider. Enrollees who fill a prescription may have a co-payment of between $1-$5. Participants can also buy nicotine replacement products out-of-pocket, which are available over-the-counter (i.e., patch, gum, lozenge). Additionally, all residents of Minnesota can access free tobacco treatment counseling from the state quitline ([name]).

In sum, participants assigned to usual care are able to receive the same or similar smoking cessation treatment components (including pharmacotherapy and telephone counseling) as those given to participants in the proactive care intervention group. What differs is that participants in the proactive intervention are specifically invited – through the methods of proactive outreach -- to consider treatment for tobacco dependence, and given facilitated access to treatment options, whereas participants in the usual care intervention must self-initiate access to treatment.

### Proactive care intervention

The proactive tobacco treatment intervention is based on social cognitive theory (SCT) [22], the stages of change model [23] and the biopsychosocial model of perceived discrimination [24]. Proactive care through mailed invitation materials, outreach calls, and the offer of free NRT along with telephone counseling is expected to largely address provider and patient barriers to initiating care. The proactive care intervention combines two primary components: 1) proactive outreach (a mailed invitation letter followed by telephone outreach) and 2) facilitated access to comprehensive, evidence-based smoking cessation treatment (free telephone counseling and free NRT). Participants are able to choose from one of three over-the-counter NRT products (nicotine patch, gum, or lozenge).

